## **3.5 Treatment Assignment Procedures**

### **3.5.1 Randomization Procedures**

Individual participants will be randomized to receive either 30µg or 100µg of GMZ2 or rabies vaccine. Randomization to any of the three groups will be done based on a list of eligible participants identified after screening is completed. The randomization list generated by the statistician will ensure that the random allocation has a fairly even distribution of sex and age in the groups. The randomization list will contain sequential codes linking a study number to a vaccine assignment. Study numbers will be assigned to participants of each cohort in the order in which they are enrolled in the trial. Access to the randomization list will be exclusively limited to the vaccine administrator/pharmacist(s) and the study statistician. These individuals will be unblinded and will not be involved in any of the study participants' evaluation. The independent Local Safety Monitor will also keep one set of the randomization code in a sealed envelope, for the event when emergency unblinding may be required.

### **3.5.2 Masking Procedures**

Measures will be taken to keep participants and clinical investigators (including the PI) and all other staff involved in measuring study outcomes blinded to treatment allocation. The GMZ2 vaccine and the rabies vaccine will have different appearances. Therefore, blinding of the individual preparing the study vaccine will not be possible. Since the candidate and comparison vaccines can be distinguished by appearance, the vaccine preparation area and the vaccination area will be physically separated. The vaccine administrator and assistant, both experienced and trained pharmacists, will be exclusively dedicated to vaccine preparation.

The syringe barrels will be covered with opaque tape. Vaccinators will be physicians and nurses not directly involved in evaluation/follow up of participants, so that even if they realize which vaccine they are injecting, they will not be involved in the assessment of adverse events following vaccination. Each participant will be vaccinated in a closed room out of view of anyone other than the vaccinators, so that each participant sees only the syringe he is injected with and do not see other participants being injected. Evaluation of immediate adverse events will be done in the observation room by clinicians who will remain blinded to the vaccine administered.

### **3.5.3 Reasons for Withdrawal**

The following criteria will be checked at each visit. If any become applicable during the study, the participant will not be required to discontinue the study, but a separate immunogenicity analysis may be done that excludes these individuals.

- Use of any investigational drug or vaccine other than the study vaccine(s) during the study period.

[figure not shown]

- Chronic administration (defined as more than 14 days) of any dose level of immunosuppressants or other immune-modifying drugs during the study period and chronic daily use of inhaled steroids. Intermittent use of inhaled and topical steroids is allowed.
- Administration of a vaccine not foreseen by the study protocol during the period starting from 30 days before the first study vaccination and ending 30 days after the third vaccination.
- Administration of immunoglobulins and/or any blood products up to 30 days after the last study vaccination.

The following criteria will be checked prior to each vaccination and are contraindications to further vaccination. However, the study participants will be encouraged to continue to participate in the surveillance schedule for safety evaluation.

- Systemic hypersensitivity reaction following administration of the study vaccine. Severe (i.e., Grade 3) local reactions will be evaluated to determine whether or not further study vaccinations should be administered.

Participants may also withdraw voluntarily from receiving the study intervention upon request for any reason.

### 3.5.4 Handling of Withdrawals

Every effort will be made to collect safety data on any participant discontinued because of an AE or SAE by continuing the safety follow-up procedures. If voluntary withdrawal occurs, the participant will be asked to continue scheduled evaluations and be given appropriate care under medical supervision until the symptoms of any AE resolve or the participant's condition becomes stable. If possible, participants who leave the study area will be traced and visited by clinical investigators to collect all possible safety follow-up data.

### 3.5.5 Termination of Study

The trial may be terminated by the sponsors or the PI due to development of serious laboratory toxicities or other major safety concern identified during interim safety analyses by the DSMB or at any other time.

**“Any subject who does not finish the trial must be classified based on the following categories: discontinuation, voluntary withdrawal (or drop-out), lost to follow-up”.**

### 3.5.6 Definitions

Discontinuation by the investigator: the decision to terminate the participant's participation was taken by the investigator e.g. for medical reasons (for participant's safety), for practical reasons (non respect of study schedule), serious adverse event, etc

[figure not shown]

Voluntary withdrawal or Drop-out: a participant included in the trial is said to have dropped out after legal consenting guardian deciding, on his/her own volition, to terminate participation of the child in the trial.

The participant's guardian may decide to withdraw from the trial at any time. The investigator should make sure, however, that withdrawal was not due to an adverse event. The reason for withdrawal should be noted in the space provided for this purpose in the Case Report Form (CRF).

Lost to follow-up: when the participant could not be found in spite of the investigator's efforts to locate him. If the participant is rediscovered later on, efforts would be made to collect all possible safety information.

[figure not shown]

## 4 INTERVENTION/INVESTIGATIONAL PRODUCT

### 4.1 Study Product Description

#### 4.1.1 Description

The GMZ2 is a recombinant vaccine. The fusion protein of vaccine interest is a hybrid of MSP3 and GLURP antigens. After expression of the protein in *Lactococcus lactis* system, GMZ2 is purified and lyophilised. The vaccine is presented in multi-dose vials, and has an aspect of white amorphous powder.

#### 4.1.2 Formulation

Active ingredient: (GMZ2): 129, 50 µg/ml (1 ml/vial)

Other ingredients: 10 mM KH2PO4 + 137 mM NaCl + 0,6% sucrose, pH 6,5

#### 4.1.3 Manufacturer

The GMZ 2 vaccine has been manufactured by Henogen S.A in Belgium.

#### 4.1.4 Preparation

The vaccine will be reconstituted with adjuvant. Appropriate preparation protocol will be developed that will constitute SOP for preparing 0.5mL solutions that contain either 30µg or 100µg depending on vaccine allocation as dictated by study ID numbers. The reconstitution with adjuvant will be performed under sterile conditions. The adjuvanted solution will be aliquoted in disposable vanish point syringe for a single use with a 25 mm, 23 gauge single-use needle.

#### 4.1.5 Aluminium hydroxide formulation:

Alhydrogel® is a crystalline aluminium oxyhydroxide AlO2H, known mineralogically as boehmite. The structure consists of corrugated sheets of aluminium octahedra. The concentration used for the candidate vaccine is 1.7mg/ml Al3+.

#### 4.1.6 Precaution for use

A separate sterile vanish point syringe will be used for each individual trial participant to prevent transmission of infectious agents. Before injection, the site of injection will be cleansed with a suitable antiseptic and the entire content of each syringe should be used. Do not inject in a blood vessel. As for any injectable vaccine, appropriate equipment will be available in case of immediate allergic reactions.

### 4.2 Vaccination

Enrolled participants will receive three injections of a vaccine by intramuscular route into the deltoid muscle region, left arm at the first and third injection, and right arm will be given the second injection. Caution will be taken to ensure that the injection does not go into a blood vessel. The site of injection will be recorded on the case report form.

[figure not shown]

### 4.3 Prior hand Concomitant Therapy

Immunosuppressive or immuno-modulator treatments are exclusionary criteria. If it happens to be necessary to use one of them during the trial period, the data of the concerned volunteers will be considered as deviation to the protocol. Antipyretics or analgesics will not be allowed as preventive treatment of pain or fever, before the vaccination.

Other vaccinations will not be allowed during a three month period before the first trial vaccine injection and within six months after the third trial vaccine injection. If a vaccination is necessary during the banning time window, the data of the subjects will be considered as deviation to the protocol.

For all other treatment, the following data will be specified and recorded on Case Report Forms:

- Trade name and generic name
- Total daily dose
- Start and stop dates (and, if appropriate, timing requirements within the day: AM, PM, post-shot)
- Indication

### 4.4 Management of Vaccines- GMZ2

#### Labelling and Packaging

The multi-dose vaccine vials will be labelled with a standard label, mentioning that the vaccine use is restricted to clinical trial.

The reconstituted vaccines in syringes will be labelled using the model below:

|                                                     |
|-----------------------------------------------------|
| ____µg dose (Group ____)                            |
| Trial: GMZ2_03_08                                   |
| (____) doses Intramuscular (1 dose = 0.5 ml)        |
| Store between +2 and +8° C.                         |
| Expiry (date & time): (____ hours from mixing time) |
| Contact person: [name]                  |
| [contact]                                 |
| For clinical trial use only                         |

### 4.5 Storage and Shipment Conditions

A qualified pharmacist will be personally responsible for product management. The vaccines will be shipped to the study centre according to the pre-determined schedule which will be based on estimated study start date, and only after the written ethics approval for the study has been received at AMANET.

The pharmacist will be expected to return to the Sponsor a completed dispatch note which will be attached to the package, as acknowledgement of receipt. The person in charge of product receipt will check that the cold chain was maintained during shipment. In case of a problem, he/she should alert the Clinical Monitor immediately. The acknowledgement of receipt will be

[figure not shown]

dated and signed by the person in charge of product management. One copy will be kept archived, the other copy will be returned to the trial sponsor AMANET.

GMZ2 vaccine will be stored at a temperature of -20°C. Reconstituted vaccines will be stored at temperatures ranging from +2°C to +8°C (in a refrigerator). Temperature will be monitored daily and documented on an appropriate form during the entire trial. The reconstituted vaccines should be administered within 24hrs.

In case of deep freezing or accidental disruption of the cold chain, vaccines should never be administered and the investigator or the responsible person should contact the sponsor immediately to receive further instructions.

The rabies vaccine (Verorab) will be stored according to manufacturer's instructions between +2 and +8°C.

#### **4.6 Accountability**

Products must be kept in a secure place. The pharmacist in charge of product management will maintain records of the product's delivery to the trial site, the inventory at the site, the dose(s) given to each subject, and the return of unused doses to the sponsor. The applicable sponsor vaccine accountability log shall be kept up to date at all times.

Should the investigator run out of product doses during the trial, he/she should alert the Clinical Monitor who will undertake the necessary steps to ensure that extra doses available in time for the next vaccinations.

#### **4.7 Return of Unused Products**

Unused and/or open products will be returned to AMANET at the end of the vaccination period together with the form "Return of unused and/or open products" in accordance with the Monitor's instructions.

#### **4.8 Concomitant Medications/Treatments**

At each study visit/contact, the investigator will question the guardians about any medication that may have been given to the participant, including traditional medicines. Concomitant medication, including any vaccine other than the study vaccines, and any other medication relevant to the protocol, including any specifically contraindicated or administered during the period starting from one week before each study vaccination and ending one month (maximum 30 days) after will be recorded in the CRF with trade name and/or generic name of the medication, medical indication, start and end dates of treatment.

[figure not shown]

## 5 PARTICIPANT PROCEDURES

### 5.1 Screening Day –14 to –1

The accepted process of reaching the community that has been established over the years between MRU and Lambaréné community will be followed. This requires that after the protocol is approved by the authorities, special information dissemination meetings are held starting with the key civic and traditional leaders. Awareness campaigns are then undertaken including peer communication groups before the reaching the stage of small groups of potential participants, and finally individuals.

After community information is disseminated as described, all interested guardians of potential participants will be invited to visit the study clinic on a specific date. They will receive oral and written explanation of the study, after which the screening consent will be obtained from those willing to participate. After the study has been explained to the parents/guardians of potential participants, they will be free to leave and return later with their decision; this will allow time for them to discuss the study with their family and carefully consider their involvement in the study.

All screening tests, medical history and examinations will be performed only after screening consent is obtained. Clinical Investigators will generally handle acute, simple conditions such as malaria or other acute infections. More complicated or chronic conditions, such as chronic renal or heart disease, will be referred to appropriate sources of medical care.

It is estimated that 50-60 children will be screened in order to obtain a list of at least 40 eligible participants. Participants will be recruited among children residing in Lambaréné.

A screening form will be prepared for each participant and will later become part of the CRF for participants enrolled in the vaccine trial. A unique screening identification number will be assigned to each study participant. A medical history will be taken with special attention to recurrent infections to suggest immune suppression, previous history of splenectomy and prior vaccine reactions. Physical examination and laboratory screening tests will include: full blood count (FBC), creatinine, total bilirubin, ALT, AST, alkaline phosphatase. A participant who meets any of the exclusion criteria will be excluded. Participants excluded from this study because of significant abnormalities will be managed initially by Clinical Investigators and may be referred to the hospital for further evaluation as may be necessary. Screening tests will be completed within 14 days prior to entry into the study. Laboratory studies may be conducted at other times during the course of the trial if the investigators judge it necessary for the safety of the participant.

#### **Visit 1 (may take place over more than one visit)**

- Written informed consent for screening
- Medical history of participant
- Complete physical examination
- Collect 5 ml venous blood sample to measure:

[figure not shown]

- Haematology: Full Blood Count (FBC) which includes: red blood cells, platelets, white blood cell count, lymphocyte count, haemoglobin, mean corpuscular volume and mean corpuscular haemoglobin concentration, haematocrit (2.5 ml).
- Biochemistry: serum creatinine, total bilirubin, ALT, AST, alkaline phosphatase (2.5 ml).
- Blood smear for malaria parasites
- Check for inclusion and exclusion criteria
- Written informed study consent for vaccination

## 5.2 Enrolment/Baseline

When a total of 40 eligible participants are screened, a list with their screening numbers, dates of birth and sex will immediately be generated and transmitted to the study statistician based at the London School of Hygiene and Tropical Medicine. The statistician will then generate a randomisation code list that allocates study ID numbers linked to vaccine allocation. This list will be generated to ensure that an even distribution of age and sex is achieved in each of the three study groups. The statistician will then send the randomisation code list directly to the study pharmacist and local safety monitor via email with a secure password to access the list.

At the site study numbers will be assigned to participants of each cohort in the order in which they come to MRU on the day of the first vaccination. Immediately after the first vaccination, each study participant will receive a photo ID card and a copy of the photo ID will be attached to the CRF folder for each participant. The vaccine and dose that are assigned during the first vaccination will be maintained for second and third vaccinations.

Access to the randomization list will be exclusively limited to the study drug manager(s)/pharmacist(s) and study statistician. These individuals are unblinded and will not be involved in study participants' further evaluation. The Local Safety Monitor will also keep one set of the randomization code in a sealed envelope, in the event that emergency unblinding is required. The reason for any unblinding will be documented as well as the steps to be taken.

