| Study Design                         | Phase 1b double-blind, randomised, and controlled trial with three groups at one study site                                                                                                                                                                               |             |                    |               |             |
| Randomization allocation concealment | The Statistician will randomise and prepare sealed allocation envelopes based on the screened list of eligible children. Allocation list will be maintained by the Pharmacist and the Local Safety Monitor (LSM) in case of need to unblind the study for safety reasons. |             |                    |               |             |
| Estimated Time to Complete Enrolment | Two weeks                                                                                                                                                                                                                                                                 |             |                    |               |             |
| Trial Centre                         | Medical Research Unit, Albert Schweitzer Hospital                                                                                                                                                                                                                         |             |                    |               |             |
| Description of Agent or Intervention | Lyophilized                                                                                                                                                                                                                                                               | recombinant | Lactococcus | lactis | Hybrid GMZ2 |
| Dose                                 | 30 & 100µg                                                                                                                                                                                                                                                                |             |                    |               |             |

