## 6.2 Safety Monitoring Plan

### 6.2.1 Role of the Safety Monitor:

The Local Safety Monitor (LSM) will be an experienced clinician qualified to evaluate safety data from clinical trials of vaccines. He/she will not be directly involved in the clinical trial and will be based in Lambaréné. All SAEs will be reported to him/her. In exceptional circumstances, for example a death possibly related to vaccination, or under conditions as outlined in below in the safety monitoring plan, he/she will have the authority to suspend vaccination pending discussion with the sponsor and collaborators. He will hold the code-break information and under conditions as outlined below, he will have the authority to unblind individual subjects. All unblinding should be reported immediately to AMANET. The LSM will also pass on his reports to the Data Safety Monitoring Board (DSMB) regularly, during the process of the trial.

Thus the LSM's role will include:

- Acting as the study participants' advocate
- Promptly communicating relevant safety information to the DSMB
- Providing advice to the investigators on whether a set of clinical circumstances in a study warrants formal notification to AMANET and DSMB
- Providing clinical advice on any illness in study participants especially in circumstances in which treatment might influence the course of the trial
- Review all SAEs as outlined above

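### Section 5.2 gives the Local Safety Monitor a readable randomisation list, contradicting the exclusive access and sealed envelope set out in the same section and in 3.5.1

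*Protocol*

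**What the plan says.** Four places in the protocol deal with who holds the allocation code.

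- **Section 5.2, transmission:** the statistician sends the code list "directly to the study pharmacist and local safety monitor via email with a secure password to access the list".
- **Section 5.2, access:** "Access to the randomization list will be exclusively limited to the study drug manager(s)/pharmacist(s) and study statistician". The Local Safety Monitor is not in that group. The section then adds: "The Local Safety Monitor will also keep one set of the randomization code in a sealed envelope".
- **Section 3.5.1:** "Access to the randomization list will be exclusively limited to the vaccine administrator/pharmacist(s) and the study statistician", and again "The independent Local Safety Monitor will also keep one set of the randomization code in a sealed envelope", for emergency unblinding.
- **Synopsis:** "Allocation list will be maintained by the Pharmacist and the Local Safety Monitor (LSM) in case of need to unblind the study". The synopsis also has the statistician prepare sealed allocation envelopes, in the plural, without saying that these are code breaks for the monitor.
- **Section 6.2.1:** the monitor holds the code-break information and may unblind individual subjects. The monitor's tasks include "Providing advice to the investigators on whether a set of clinical circumstances in a study warrants formal notification to AMANET and DSMB". The monitor also receives and reviews all SAEs, gives clinical advice on illness in participants, reports to the DSMB and may suspend vaccination in exceptional circumstances. Section 6.2.3 likewise speaks of individual unblinding through the monitor.

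**The concern.** A sealed envelope protects the blind only if its holder does not already have the contents. Section 5.2 sends the monitor the list and the means to read it, then treats the monitor as someone who must break a seal to see it.

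The role makes this more than untidy wording. Both 3.5.1 and 5.2 attach a condition to list access: those who have it take no part in evaluating participants. The monitor's duties in 6.2.1 do not sit easily with that condition, since they include SAE review, clinical advice and the authority to suspend. If allocations are readable, those judgements could be made with knowledge of the arm, in a trial presented as double-blind with safety as its primary criterion.

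The form of the envelope raises a second question. The protocol wants children unblinded one at a time, but describes a single set of the code in a single envelope.

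**Working it through.** No sample size, power or error rate is involved, so the check sets the statements side by side.

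**Step 1: who can read the list?**

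| Place | Pharmacist | Statistician | Local Safety Monitor |
|---|---|---|---|
| Synopsis | maintains the list | randomises | maintains the list |
| 3.5.1 | access | access | sealed envelope only |
| 5.2, transmission sentence | receives list and password | sends it | receives list and password |
| 5.2, access paragraph | access | access | sealed envelope only |

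The two rows for 5.2 disagree on the monitor. Section 3.5.1 agrees with the 5.2 access paragraph. The synopsis is closer to the transmission sentence. The monitor cannot both hold list and password and be outside an exclusive access group.

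**Step 2: how many allocations are involved?** Section 8.2 gives three groups of 10, so 3 × 10 = 30. The randomisation list covers all of them.

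**Step 3: would a look at the list be traceable?** Section 5.2 requires the reason for any unblinding to be documented, and 6.2.1 requires all unblinding to be reported at once to the sponsor. Opening a sealed item gives those duties something to attach to. Reading an emailed file breaks no seal and does not show which child was looked up, so compliance could not be verified.

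**Step 4: where does the monitor's judgement meet the primary data?**

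- Under 6.2.1 the monitor reviews SAEs, advises on illness and may suspend vaccination.
- Under 6.3.10 the monitor, as well as the investigators, may judge that a child needs hospitalisation. Inpatient hospitalisation is an SAE criterion in 6.1.4, and SAEs are part of the primary criterion in 7.1.1.
- With 10 children per group, one child with an event is 1/10 = 10 percentage points of that group's frequency. This shows how much one event weighs; it does not estimate a bias.

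**Step 5: what does opening the envelope disclose?** Sections 3.5.1 and 5.2 describe one set of the code in one envelope. Sections 6.2.1 and 6.2.3 foresee unblinding of individuals. No section gives the monitor a code break per child. Read literally, opening the envelope for one child would disclose others, up to all 30 if the set is the full list on one sheet. That last step is inference, because the protocol does not say how the set is packaged.

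**The case against.** The monitor's custody of the code is deliberate. The synopsis and 6.2.1 both intend it, and someone local must be able to unblind in an emergency. The list is password-protected. Email may simply be the route and the envelope the form of storage. That is a possible reading, but the protocol gives the password to both recipients and names nobody else who would print and seal the monitor's copy. The custody point stands; the contradiction remains.

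A reader might infer that relatedness and escalation decisions are compromised. The documents do not support that:

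- Section 6.3.4 gives the causality assessment to the investigator and treats all solicited local reactions as related by rule.
- Section 3.5.2 keeps investigators and staff measuring outcomes blinded.
- Section 6.3.7 requires SAEs to reach the sponsor's contact within 24 hours.
- Section 6.2.2 requires the investigator to inform the DSMB of SAEs and Grade 3 events whatever their relationship to vaccine.
- Section 6.2.3 makes activation of the holding rules depend on DSMB review of blinded data and discussion with the investigator and sponsor.
- Section 6.2.1 places the monitor outside direct involvement in the trial, and nothing has the monitor passing on allocations.

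What remains is the monitor's own discretion in clinical advice, hospitalisation and initial suspension.

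A reader might also infer that one emergency code break certainly exposes all 30 children. The text does not establish this. The packaging is unstated, the synopsis mentions envelopes in the plural, and 6.2.1 and 6.2.3 speak of individuals. The literal wording permits that outcome without fixing it.

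**Conclusion.** The contradiction is real and lies within section 5.2 itself, with 3.5.1 on one side and the synopsis on the other. Carrying out the email step would let the Local Safety Monitor read all 30 allocations with no seal broken and no record, which defeats the sealed arrangement the protocol chose for that role. This assumes only that the email is sent as described and that the password works for the monitor as a named recipient.

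The envelope point is secondary and conditional. One set in one envelope, taken literally, does not deliver the individual unblinding that 6.2.1 and 6.2.3 call for.

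The effect on primary safety results cannot be put as a number and is at most indirect, given blinded causality assessment and mandatory reporting. The change is still worth making before the list is generated, because a disclosed list cannot be withdrawn.

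**What to change.** - In 5.2, have the statistician send the readable list to the study pharmacist only.
- Have the statistician, or the pharmacist who is already unblinded, prepare code breaks for the Local Safety Monitor, sealed individually by study number. Since the statistician is off-site, preparation by the pharmacist may be the simpler route.
- State that each code break is logged when opened, so that the documentation duty in 5.2 and the reporting duty in 6.2.1 can be checked.
- Align the synopsis, 3.5.1, 5.2 and 6.2.1 on who holds the list, who holds code breaks, and in what form.

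The cost is 30 sealed items, a log and a few sentences of protocol text. The monitor can still unblind any child at once. No vaccination procedure, holding rule or analysis changes.
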